#### Course evaluation

In absence of a standardised measure for evaluating course satisfaction in internet-based treatments, user satisfaction will be measured with a self-designed questionnaire based on the Client Satisfaction Questionnaire (CSQ-8
[47], German Version
[48]). This self-report scale consists of 8 items measuring the global client satisfaction with the internet-based training. Previous research indicated a high internal consistency
[48].

#### Response

To determine the numbers of participants achieving a reliable positive outcome we will code participants as responders or non-responders according to the widely used reliable change Index (RCI
[49]). Participants will be considered responders, when they display a RCI score of above 1.96. To determine potential negative effects of the intervention on course of symptom
[50] we will also report number of participants with reliable symptom deteriorations according to the RCI
[51].

#### Other measures

Other measurements include demographic variables (e.g., age, gender, occupation etc.), the Effort Reward Imbalance Questionnaire – Short Form (ERI-SF)
[52], the emotion regulation skills questionnaire (ERSQ)
[53, 54]. Big Five Inventory (BFI-10)
[55], Volitional Components Questionnaire – Short Form
[56], General Self-Efficacy Scale
[57], Self-Regulation Scale
[58], Self-Control Scale (SCS-K-D)
[59, 60], Psychotherapy Motivation Questionnaire – Short Form
[61, 62], Health Action Process Approach Questionnaire (HAPA-Questionnaire) (according to the guidelines by
[63]), Internet Affinity Questionnaire
[64] and the Connor-Davidson Resilience Scale (CD-RISC)
[65]. To assess presenteeism, we used the Work Limitations Questionnaire (WLQ-8)
[66], the Single-Item Presenteeism Question
[67] and a single item question on work ability
[68]. Approximately 40 minutes will be required to complete all questionnaires at baseline, and approx. 20 minutes at follow-ups. For an overview of all outcome measures, see Table 
2.

**Table 2 Tab2:** **Measures**

	T0	T1	T2	T3
Perceived stress scale	✓	✓	✓	✓
Center for epidemiological studies depression scale	-	✓	✓	✓
Maslach burnout inventory – emotional exhaustion	-	✓	✓	✓
Emotion regulation skills questionnaire – general distress	-	✓	-	-
Utrecht work engagement scale	-	✓	✓	✓
Trimbos/iMTA questionnaire for costs associated with psychiatric illness	-	✓	-	✓
EuroQol, SF-12 quality of life	-	✓	-	✓
Other measurements				
Demographic variables questionnaire	✓	-	-	-
Effort reward imbalance questionnaire – short form	-	✓	✓	✓
Client satisfactory questionnaire	-	-	✓	-
Potential dropout reasons	-	-	✓	-
Big five inventory – short form	-	✓	-	-
Volitional components questionnaire – short form	-	✓	-	-
General self-efficacy scale	-	✓	-	-
Self-regulation scale	-	✓	-	-
Self-control scale	-	✓	-	-
Psychotherapy motivation questionnaire – short form	-	✓	-	-
HAPA-questionnaire	-	✓	-	-
Internet affinity questionnaire	-	✓	-	-
Work limitations questionnaire	-	✓	✓	✓
The single-item presenteeism question	-	✓	✓	✓
A single item question on work ability	-	✓	✓	✓
Connor-Davidson resilience scale	-	✓	✓	✓

Note. T0 = Screening, T1 = Baseline, T2 = 7 weeks, T3 = 6 months.

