#### Assessment of eligibility and randomisation

People who apply for study participation will receive an online information letter with detailed information about the study procedures and will be asked to provide an e-mail-address and a first and last name (which can be pseudonyms if desired) to participate. They will be informed that they can withdraw from the intervention and/or study at any time without any negative consequences. Applicants who continue to participate in the study will be asked to complete online screening questionnaires that assess the severity of their stress level (PSS ≥ 22), and to state whether they have a high suicidal risk (BDI Item 9 > 1) and whether they have been diagnosed with psychosis or dissociative symptoms in the past.

Participants meeting all of the inclusion and none of the exclusion criteria who have completed the baseline assessment and returned the informed consent form will enter the study and will be randomly allocated to study conditions. Randomisation will take place at an individual level. The allocation will be performed by an independent researcher not otherwise involved in the study using an automated computer-based random integer generator (randlist). During the randomisation process, allocation will be concealed from participants, researchers involved in recruitment, and eCoaches. Participants will be informed about the outcome of the randomisation and participants in the intervention group will receive immediate access to the GET.ON Stress training. However, the participants in the control group will receive the login data required to complete the training six months later than the intervention group.

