#### Quality of life

We will use the Short Form 12 (SF-12)
[44] and the (EuroQol EQ-5D)
[45] to assess quality of life. The SF-12
[44] covers eight health domains (physical functioning, role limitations, pain, general health perception, vitality, mental health, emotional role and social functioning) and allows for the calculation of two sum scores for physical and mental health. We will also use the EQ-5D which is a widely applied, valid and reliable measurement of quality of life and consists of five items related to mobility, self-care, common activities, pain/discomfort and anxiety/depression. Furthermore, this measurement contains a visual analogue scale concerning health state valuation. The EQ-5D is only assessed for use in the health economic evaluation and is no secondary outcome itself.

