#### Cost-effectiveness and cost-utility analyses

In the cost-effectiveness analyses, treatment response (reliable positive change) will be the primary outcome, whereas quality adjusted life years (QALYs) will be the outcome in the cost-utility analyses. A cost-effectiveness acceptability curve
[72] will be calculated, when better outcomes are associated with higher costs. Such an acceptability curve represents the probability that the intervention is cost-effective relative to the control group, given varying thresholds for the willingness to pay (WTP) for gaining one additional treatment responder or gaining one additional QALY. Nonparametric bootstrapping will be applied to estimate confidence intervals for mean differences in costs and effects between groups.

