#### Incremental net-benefit regression analysis

Effect modification can be studied in the context of a health-economic evaluation to address the question if there are any baseline factors (i.e. subgroups of employees) associated with particularly favourable cost-effectiveness when the experimental intervention is offered. The data analytic approach taken here consists of incremental net-benefit regression analysis (INBRA). First, incremental net-benefits, Δ(NB), are calculated as *Δ*(NB) = WTP × *Δ*(QALY) - *Δ*(Costs), where WTP × Δ(QALY) is the willingness to pay for gaining one QALY and Δ(Costs) are the extra costs owing to offering the intervention. Δ(NB)s are calculated for each participant in the dataset and can then be analysed in a regression framework. In its simplest form the incremental net-benefits are regressed on the treatment indicator variable to evaluate the cost-effectiveness of the intervention relative to the control condition. When Δ(NB) exceeds €0, then the intervention is deemed to be cost-effective. The regression models can be expanded to include interaction terms of the treatment indicator variable and putative effect modifiers
[74, 75].

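### EQ-5D is not collected at 7 weeks, so QALYs rest on baseline and 6 months alone and would understate a utility gain already present at the end of training

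*Protocol article*

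**What the plan says.** The footnote to Table 2 of the protocol article defines the assessment times: "Note. T0 = Screening, T1 = Baseline, T2 = 7 weeks, T3 = 6 months". The row "EuroQol, SF-12 quality of life" is ticked at T1 and T3 and carries a dash at T2. The perceived stress, depression, emotional exhaustion, work engagement, presenteeism and resilience scales are all ticked at T2, so an online assessment does take place then.

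Under Quality of life, the article gives the only purpose of the instrument: "The EQ-5D is only assessed for use in the health economic evaluation and is no secondary outcome itself". Under Cost-effectiveness and cost-utility analyses, "quality adjusted life years (QALYs) will be the outcome in the cost-utility analyses". QALYs also enter the incremental net-benefit regression, where WTP × Δ(QALY) "is the willingness to pay for gaining one QALY".

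Baseline precedes allocation: participants "who have completed the baseline assessment and returned the informed consent form will enter the study and will be randomly allocated". The waiting-list group receives the training six months later, so the contrast with the control group runs through to T3. The primary outcome is perceived stress at post-treatment, and the sample size is built on the effect at that time.

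**The concern.** The trial expects its main effect at 7 weeks but measures utility only before randomisation and at 6 months. With two points, the course in between is assumed. A straight line from baseline to 6 months describes a benefit that builds slowly and reaches its full size only at the end. The article describes something else: core training of about 4 to 7 weeks, with the primary comparison at week 7.

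If the benefit is already there at week 7, the straight line credits too little of it. The article treats the intervention as cost-effective when the incremental net benefit exceeds €0, and it says that the economic evaluation supports decisions and does not test hypotheses. A QALY difference that is too small goes directly into that decision, while the costs of the intervention are charged in full. No later analysis can recover utilities that were not collected.

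**Working it through.** The article gives no QALY figure, so there is none to reproduce. The check compares a two-point QALY with a three-point one.

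**Inputs**
- Times: T1 = week 0, T2 = week 7, T3 = 6 months (Table 2 footnote). Six months is taken as week 26, so T2 is at 7/52 = 0.1346 years and T3 at 0.5 years.
- QALY method: area under the utility curve with straight lines between measurements. This is an assumption.
- Between-arm utility gain: 0 in expectation at T1 (randomisation), D at T2, r × D at T3. The article gives no utility data, so r is varied. The percentages do not depend on D.

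**Weights**
- Two points: QALY = 0.25 × U(T1) + 0.25 × U(T3), that is 50% / 0% / 50% on T1 / T2 / T3.
- Three points:
  - T1: 0.1346/2 = 0.0673
  - T2: 0.5/2 = 0.2500
  - T3: (0.5 − 0.1346)/2 = 0.1827
  - As shares of 0.5 years: 13.5% / 50.0% / 36.5%.

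**Between-arm gain**
- Two points: 0.25 × r × D.
- Three points: (0.25 + 0.1827 × r) × D.
- Share missed = 1 − 0.25r / (0.25 + 0.1827r).

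| r (share of week-7 gain present at month 6) | Three-point gain | Two-point gain | Missed |
|---|---|---|---|
| 1.5 | 0.524 D | 0.375 D | 28% |
| 1.2 | 0.469 D | 0.300 D | 36% |
| 1.0 | 0.433 D | 0.250 D | 42% |
| 0.75 | 0.387 D | 0.188 D | 52% |
| 0.5 | 0.341 D | 0.125 D | 63% |
| 0.25 | 0.296 D | 0.063 D | 79% |
| 0 | 0.250 D | 0 | 100% |

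**Two thresholds**
- Half is missed when 0.25r = 0.5 × (0.25 + 0.1827r), so r = 0.125/0.1587 = 0.79.
- Nothing is missed when 0.25r = 0.25 + 0.1827r, so r = 0.25/0.0673 = 3.7. This is growth along a straight line from week 0 to week 26 (26/7 = 3.7).

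**Effect on net benefit.** At r = 1 the two-point QALY difference is 0.25/0.4327 = 0.578 of the three-point one. In Δ(NB) = WTP × Δ(QALY) − Δ(Costs), this has the same effect as cutting the willingness to pay by 42% with the cost term unchanged.

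**The case against.** **The size depends on what happens after week 7.** The article gives no utility trajectory. It also plans a booster session four weeks after the core training, which for a participant finishing at week 7 falls around week 11, and it stresses transfer into daily life. Some growth after T2 is therefore possible and would bring the loss below 42%. This stands. A reader might infer that an early effect is mostly lost in any case, but the loss exceeds one half only if less than about 79% of the week-7 gain remains at 6 months.

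**The QALY formula is assumed.** An article may leave it to the full plan, and its absence is no fault. Whatever the formula, no utility is measured between T1 and T3, so the path has to be assumed.

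**The direction is conservative** for superiority over the waiting list. That is true, but the economic analysis is meant to inform a decision, and there an understated benefit is still an error.

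**Baseline value.** A reader might infer bias because half of a two-point QALY is the pre-randomisation value. Under randomisation that half cancels between arms in expectation. Chance imbalance adds noise, which the bootstrap intervals reflect. The article's silence on baseline adjustment is detail that an analysis plan may hold.

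**Cost questionnaire.** "Trimbos/iMTA questionnaire for costs associated with psychiatric illness" is also skipped at T2, and a reader might infer that costs during the programme are lost. The article states no recall period, so this is not shown. The questionnaire also has no bearing on QALYs.

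**T2 is the primary-endpoint assessment**, and keeping it short is a reasonable aim. This bears on where the items are placed more than on whether five items can be added.

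**Conclusion.** The point holds in a limited form and is a cheap improvement. The schedule in Table 2 leaves no utility value at the time of the expected effect. With straight-line area under the curve, a gain present at week 7 is understated by about 42% if sustained to month 6, 63% if halved, and 100% if gone. Growth after week 7 makes the loss smaller, and it reaches zero at about 3.7 times the week-7 gain. These figures rest on the assumed QALY method, on 6 months being week 26, and on a three-point path that is itself straight between measurements.

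The reach is limited to the cost-utility analysis and the exploratory net-benefit regression. The primary outcome, the cost-effectiveness analysis based on treatment response and the employer's cost-benefit analysis do not use QALYs. The documents do not support a claim of bias from the baseline value or of lost cost data.

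**What to change.** In Table 2, add EQ-5D at T2, and calculate QALYs from T1, T2 and T3. Place the five items after the PSS so that they cannot disturb the primary outcome. SF-12 can stay at T1 and T3.

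The cost is a slightly longer T2 questionnaire, on top of an online follow-up that already takes about 20 minutes.

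For participants for whom T2 has already passed, the value cannot be recovered. In that case, state the QALY method and report a sensitivity analysis over the possible courses between T1 and T3, such as the values of r in the table above.

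Adjusting the QALY difference for T1 utility is optional. It can improve precision, and nothing in this point depends on it.

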### Sample size calculation

We aim to include 408 participants. The study was designed based on the expected superiority of the active groups (minimal guided and unguided internet-based self-help) compared to the waiting-list control group on the primary outcome variable (i.e. perceived stress) at post-test. Based on pilot-evaluation data we expect a mean effect for the minimal guided treatment arm compared to the waiting list control group of d = 0.70. However, unguided internet-based interventions consistently produce lower effect sizes as guided interventions
[15] and a meta-analysis on traditional face-to-face interventions for work-related stress
[6] yielded an overall combined effect size of only d = 0.34. As we also want to examine the difference in the effectiveness of minimal guided and the unguided iSMI we aim to be able to detect difference between groups with an effect size of d = 0.30. Thus we need to include 408 participants. This sample will allow us to detect a between-group effect size (ES) of d = 0.30 with a power (1-ß) of 80 % and an alpha of .05 (calculated using PASS 12) in a one-tailed test (for uni-directional hypotheses H1: WLC < unguided < minimal guided iSMI).

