Although it is often assumed that Internet-based interventions offer good value for money, evidence for their cost-effectiveness from randomised trials is still scarce and, to the best of our knowledge, completely absent when it comes to internet-based SMI in the work setting. Studies currently investigating the cost-effectiveness of mental health interventions for workers include a study on a guided self-help course for workers with depressive symptoms
[23] and a study on a guided self-help regeneration training for stressed employees with work-related rumination and sleeping problems
[24]. Our group recently conducted a randomised controlled trial testing the efficacy and cost-effectiveness of an internet-based SMI in employees with heightened levels of perceived stress
[25]. Results are still pending. However, that latter study only evaluated an intervention including substantial professional support (up to 4 h per participant) which is thus very time-consuming and expensive. This clearly limits the possible reach of the intervention and, consequently, its potential to reduce the negative consequences of occupational stress at population level. Once developed, costs of internet-based interventions are substantially linked to professional guidance time. Thus, evaluating whether interventions with less intensive guidance up to 1 h per participant (minimal guidance, or unguided interventions) may still be effective appears promising.

Internet-based mental health interventions without guidance are often much less effective than interventions including at least some guidance from a professional
[15, 16]. However, direct comparisons in randomised controlled trials are scarce. A recent systematic review identified only five of such randomised trials evaluating internet-based interventions for mental health related problems (Reichler et al. in prep). Guided interventions were significantly superior to unguided interventions (d = 0.22). Nevertheless, despite the possibly lower effectiveness of unguided interventions compared to guided interventions, unguided self-help may still produce larger effects at a population level with regard to the reduction of disease burden, given that more individuals can be reached for comparable costs. However, to the best of our knowledge, no study on the comparative efficacy and cost-effectiveness of guided and unguided SMI has been published so far.

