## Methods

### Design

A three-armed randomised controlled trial (RCT) will be conducted to compare minimal guided and unguided iSMI (GET.ON Stress) with a waiting list control condition (WLC). All intervention arms will have full access to treatment as usual (TAU). To control for potential confounding effects, TAU will be monitored. Assessments will take place at baseline (T1), post-treatment (7 weeks, T2), and at 6-months follow-up (T3; see Figure 
1 for a detailed overview of assessments). All procedures involved in the study will be consistent with the generally accepted standards of ethical practice. The study was approved by the University of Marburg ethics committee (No. 2014-5K). The trial is registered in the German clinical trials register under DRKS00005687.

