### Statistical analyses

#### Clinical effectiveness

The trial will be conducted in compliance with the study protocol, the Declaration of Helsinki and GCP. Aiming at an intention-to-treat design we will include all participants who will be randomly assigned to conditions. Additionally, per protocol analyses (PPA) will be conducted, including only participants’ satisfying protocol treatment. Analyses of variance will be conducted to explore the effects of the treatments on all primary and secondary outcomes. Missing data will be handled using multiple imputations (MI). MI is especially robust with respect to missing data
[69]. For all analyses, Cohen’s d
[70] will be calculated by standardising the differences between baseline and follow-up scores by the pooled standard deviation of the baseline scores. We will also calculate the number needed-to-be-treated (NNT) with GET.ON Stress minimal guided and unguided to achieve one response compared to the control group. For all statistical analyses, significance level will be set at p < .05, one-sided. The effectiveness evaluation will be conducted in accordance with the CONSORT statement
[71].

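### The 80% power at d = 0.30 holds only if all 408 participants give post-test PSS data; the sample size has no allowance for attrition

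*Protocol article*

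**What the plan says.** **Sample size calculation.** The target is stated as "We aim to include 408 participants". The effect size that fixes it comes from the wish to compare the two active arms: "we aim to be able to detect difference between groups with an effect size of d = 0.30". The claim for the resulting sample is "This sample will allow us to detect a between-group effect size (ES) of" "d = 0.30 with a power (1-ß) of 80" %, at alpha .05 in a one-tailed test. The number needed and the number to be included are the same, 408. The section gives no attrition rate, inflation or baseline-outcome correlation.

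**Design.** "A three-armed randomised controlled trial (RCT) will be conducted to compare minimal guided and unguided iSMI" with a waiting list. The allocation ratio is not stated.

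**Assessment of eligibility and randomisation.** Applicants are told that they may leave the intervention, the study or both at any time.

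**Statistical analyses, Clinical effectiveness.** All randomised participants are to be included, using analyses of variance at a one-sided 5% level. On incomplete data: "Missing data will be handled using multiple imputations (MI"). No baseline covariate is named.

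**Primary and secondary outcomes.** The primary outcome is perceived stress at post-treatment (7 weeks).

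**The concern.** The power claim is attached to the number included, but power depends on the information in the observed post-test scores. If 408 is exactly what the calculation needs with nobody missing, the claim rests on a condition that the article's own withdrawal and missing-data provisions do not assume.

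The contrast at stake is the one that set the sample size: minimal guided versus unguided, aim 2 in the Aims section and the basis of the value-for-money question. The Discussion repeats that the study is powered for between-group differences. A reader who weighs a non-significant aim 2 result against an advertised 80% would give it more weight than the design supports.

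**Working it through.** **Inputs**

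- N = 408, d = 0.30, power 80%, alpha 0.05 one-tailed (Sample size calculation). The one-sided 5% level is repeated under Clinical effectiveness.
- Three arms (Design). Equal allocation is assumed: 408 / 3 = 136 per arm.
- Attrition: no rate is given, so 5%, 10%, 20% and 30% are assumed.
- Baseline-outcome correlation r: not given, so 0.3, 0.4 and 0.5 are assumed where it is needed.

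**Step 1: reproduce the stated figure.** For two arms of n each, df = 2n − 2, the noncentrality is λ = d√(n/2), and power = P(T(df, λ) > t(0.95, df)).

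With n = 136: λ = 0.30 × √68 = 2.474, df = 270, critical value 1.651, power **79.5%** (79.6% by normal approximation). This rounds to the stated 80%.

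Other readings do not reproduce it (normal approximation): two-sided alpha gives 69.6%, 204 versus 204 gives 91.7%, and both active arms pooled versus waiting list (272 versus 136) gives 88.7%. So 408 is 136 per arm, one-sided, with every outcome observed, and it holds no hidden margin.

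**Step 2: power with post-test scores missing.** Put n = 136 × (1 − m), rounded to whole participants, into the same formula. The last column solves it for the d that has 80% power.

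| Missing (assumed) | n per arm | λ at d = 0.30 | Power at d = 0.30 | d with 80% power |
|---|---|---|---|---|
| 0% | 136 | 2.474 | 79.5% | 0.302 |
| 5% | 129 | 2.409 | 77.6% | 0.310 |
| 10% | 122 | 2.343 | 75.5% | 0.319 |
| 20% | 109 | 2.215 | 71.3% | 0.338 |
| 30% | 95 | 2.068 | 66.1% | 0.362 |

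**Step 3: what multiple imputation could recover.** If missing scores are imputed from baseline with correlation r, the variance of an arm mean is about σ²[(1 − r²)/n_obs + r²/n]. At 20% missing:

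- r = 0.5: 0.75/109 + 0.25/136 = 0.00872, an effective n of about 115 and power of about 73%.
- r = 0.7: 0.51/109 + 0.49/136 = 0.00828, an effective n of about 121 and power of about 75%.

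The step 2 figures are therefore approximate lower bounds, but the recovery is modest.

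**Step 4: what baseline adjustment could recover.** Adjusting for baseline raises the effective d to 0.30/√(1 − r²). At 20% missing (109 per arm):

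| r (assumed) | Effective d | λ | Power |
|---|---|---|---|
| 0.3 | 0.314 | 2.322 | 74.8% |
| 0.4 | 0.327 | 2.416 | 77.8% |
| 0.5 | 0.346 | 2.557 | 81.7% |

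**Step 5: comparisons with waiting list.** At the expected d = 0.70 for minimal guided, 95 per arm gives λ = 0.70 × √47.5 = 4.82 and power above 99%. At d = 0.34, the other effect size cited in the sample size section, power is 87.5% with complete data and 80.4% at 20% missing.

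**The case against.** **The arithmetic is not wrong.** Correct. A reader might note that strict 80% needs slightly more than 136 per arm and call 408 a miscalculation. The documents do not support that: 79.5% rounds to 80%, and the figure reproduces. The point concerns the condition attached to the figure.

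**The size of the shortfall is assumed.** Also correct. At 5% missing the loss is about two percentage points. What does not depend on the assumption is that 408 has no margin.

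**The planned analysis is not complete-case.** This stands in part. Multiple imputation recovers a little, and baseline adjustment with r near 0.5 could offset 20% missing. The article speaks of changes in perceived stress and of analyses of variance, which leaves the use of baseline open. But the power statement claims no such gain, and at r = 0.3 or 0.4 the offset is incomplete at 20% missing.

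**Table 2 as evidence of missing outcomes.** The item "Potential dropout reasons" is ticked only at 7 weeks, and a participant who answers it then is being assessed then. It may concern dropout from the training. It is weak evidence that PSS will be missing, and the point does not need it.

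**The effect size of 0.22.** The Background cites a review of direct comparisons ("Guided interventions were significantly superior to unguided interventions", d = 0.22), and a reader might infer that a target of 0.30 is contradicted. It is not. The article presents 0.30 as the difference it wants to be able to detect, and the review covers mental health problems generally. The 0.22 is context.

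**The trial as a whole is underpowered.** Not supported. The design rests first on superiority over waiting list, and step 5 shows that comparison to be safe at d = 0.70.

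**Conclusion.** The concern holds in a limited form. The stated 80% at d = 0.30 is correct only with complete post-test PSS, and the article plans for incomplete data without an allowance. Under assumed missingness of 5% to 30%, unadjusted power falls to between 77.6% and 66.1%, as approximate lower bounds. The shortfall is confined to contrasts near d = 0.30, chiefly minimal guided versus unguided.

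This rests on equal allocation, a one-sided 5% two-sample comparison, and attrition rates that are not in the document. A reader might take 71% as the trial's real power; that goes too far, because neither the attrition rate nor the use of baseline is fixed. Nor is this a detail left to a fuller document: the article makes a positive numerical claim for the number included, and an analysis plan cannot make 408 included equal 408 observed. It could supply the baseline-adjusted basis that the claim now lacks.

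**What to change.** Keep 408 and do one of the following in the Sample size calculation section.

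1. State the condition. For example: 408 randomised (136 per arm) gives about 80% power (79.5%) for d = 0.30, one-sided 5%, if all post-test scores are observed; without baseline adjustment, power is about 76% with 10% missing and 71% with 20% missing, these rates being assumptions.
2. If an unconditional 80% is to stay, base it on a baseline-adjusted analysis, name that model under Clinical effectiveness, and state the assumed correlation and attrition. With 20% missing, r = 0.5 supports the claim (81.7%); r = 0.4 (77.8%) and r = 0.3 (74.8%) do not.

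Either way, say that minimal guided versus waiting list at d = 0.70 is not affected. The cost is about two sentences and, under the first option, a less favourable figure for aim 2. No participants are added and no procedure changes.
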